## **3.0 Subject Eligibility**

Eligibility waivers are not permitted. Subjects must meet all of the inclusion and exclusion criteria to be registered to the study. Study treatment may not begin until a subject is registered.

---

### 3.1 Inclusion Criteria

- 3.1.1 Stage Tis, T1, or T2 laryngeal squamous cancer as defined by American Joint Commission on Cancer (AJCC) 2007 staging system
- 3.1.2 Biopsy proven squamous cell carcinoma histology or squamous cell variants (sarcomatoid, verrucous, basaloid, and papillary subtypes) involving the true vocal cord
- 3.1.3 Direct laryngoscopy showing no evidence of greater than Stage II true glottic larynx cancer
- 3.1.4 Chest X-ray or CT-scan showing no evidence of metastatic disease
- 3.1.5 CT-scan of the neck showing no evidence of nodal involvement
- 3.1.6 Age  $\geq 18$  years.
- 3.1.7 Women of child-bearing potential and men must agree to use adequate contraception (hormonal or barrier method of birth control; abstinence) prior to study entry, for the duration of study participation, and for 90 days following completion of therapy. Should a woman become pregnant or suspect she is pregnant while participating in this study, she should inform her treating physician immediately.
  - 3.1.6.1 A female of child-bearing potential is any woman (regardless of sexual orientation, having undergone a tubal ligation, or remaining celibate by choice) who meets the following criteria:
    - Has not undergone a hysterectomy or bilateral oophorectomy; or
    - Has not been naturally postmenopausal for at least 12 consecutive months (i.e., has had menses at any time in the preceding 12 consecutive months).
- 3.1.8 Ability to understand and the willingness to sign a written informed consent
- 3.1.9 Eastern Cooperative Oncology Group (ECOG) performance status 0-1
- 3.1.10 Negative Urine  $\beta$ -HCG or negative serum quantitative  $\beta$ -HCG or within 2 weeks prior to registration for women of childbearing potential

### 3.2 Exclusion Criteria

- 3.2.1 Evidence of fixed vocal cord (Stage cT3)
- 3.2.2 Evidence of thyroid or soft tissue invasion (Stage cT4)
- 3.2.3 Evidence of positive nodal disease (Stage N1)
- 3.2.4 Evidence of metastatic disease (Stage M1)
- 3.2.5 Subjects may not be receiving any other investigational agents.
- 3.2.6 Non-squamous histology including lymphoma, neuroendocrine carcinoma, adenocarcinoma, or other histology.
- 3.2.7 Previous laryngeal surgery.
- 3.2.8 Previous laser therapy within one year prior to protocol treatment.
- 3.2.9 Previous head and neck radiation therapy involving the glottic larynx
- 3.2.10 Patients with collagen vascular disease, specifically dermatomyositis with a CPK level above normal or active skin rash, systemic lupus erythematosus, or scleroderma.
- 3.2.11 Any prior treatment with radiation therapy or chemotherapy for the currently diagnosed larynx cancer prior to registration.
- 3.2.12 History of another active uncontrolled malignancy at the time of study enrollment
- 3.2.13 Subjects must not be pregnant due to the potential for congenital abnormalities.
- 3.2.14 Patients smoking in excess of 2 packs of cigarettes per day.
- 3.2.15 ECOG performance status  $\geq 2$
- 3.2.16 Life expectancy  $< 3$  years

## 4.0 TREATMENT PLAN

### 4.1 Treatment Dosage and Administration

- 4.1.1 This phase I clinical trial will begin with hemilarynx CyberKnife radiotherapy to a dose of 50 Gy delivered in 15 fractions. If this dose/fraction scheme has no dose limiting toxicity, there will be a reduction to 10 fractions to a bio-equivalent dose of 45 Gy. If this dose level is tolerated without dose limiting toxicity, there will be an additional reduction to 5 fractions to a bio-equivalent dose of 42.5 Gy. The patients will also be followed prospectively for voice quality and quality of life. The dose will be prescribed to provide at least 95% planning treatment volume (PTV) coverage.

| Agent         | Pre-medications;
Precautions                                                             | Dose | Route | Schedule                                |
|---------------|---------------------------------------------------------------------------------------------|------|-------|-----------------------------------------|
| Dexamethasone | Pre-medicate with Dexamethasone 1 hour prior to radiation treatments for dose level 1 and 2 | 4 mg | Oral  | Daily 1 hour prior to radiation therapy |

| Dose-Escalation Schedule |                                                                                     |                            |
|--------------------------|-------------------------------------------------------------------------------------|----------------------------|
| Dose Level               | Dose of the Study Agent(s)*                                                         | Minimum Number of Patients |
| Level -1                 | 52.5 Gy in 16 fractions of 3.28 Gy per fraction daily                               | 3                          |
| Level 0                  | 50 Gy in 15 fractions of 3.33 Gy per fraction daily, delivered 5 fractions per week | 3                          |
| Level 1                  | 45 Gy in 10 fractions of 4.5 Gy per fraction daily, delivered 3 fractions per week  | 7                          |
| Level 2                  | 42.5 Gy in 5 fractions of 8.5 Gy per fraction daily, delivered 2 fractions per week | 7                          |

| Toxicity Dose Reductions                                                                                    |                                                               |
|-------------------------------------------------------------------------------------------------------------|---------------------------------------------------------------|
| Event                                                                                                       | Action                                                        |
| Laryngeal Edema                                                                                      |                                                               |
| Grade 1 Asymptomatic; clinical or diagnostic observations only; intervention not indicated                  | None                                                          |
| Grade 2 Symptomatic; medical intervention indicated (e.g., dexamethasone, epinephrine, antihistamines)      | None                                                          |
| Grade 3 Stridor; respiratory distress; hospitalization indicated                                            | See Section 10 Statistical Considerations                     |
| Grade 4 Life-threatening airway compromise; urgent intervention indicated (e.g., tracheotomy or intubation) | Termination of trial with reporting of dose limiting toxicity |
| Grade 5 Death                                                                                               | Termination of trial with reporting of dose limiting toxicity |

|                                                                                                                                                                                        |                                                               |
|----------------------------------------------------------------------------------------------------------------------------------------------------------------------------------------|---------------------------------------------------------------|
| Voice                                                                                                                                                                           |                                                               |
| Grade 1 Mild or intermittent change from normal voices                                                                                                                                 | None                                                          |
| Grade 2 Moderate or persistent change from normal voice; still understandable                                                                                                          | None                                                          |
| Grade 3 Severe voice changes including predominantly whispered speech; may require frequent repetition or face-to-face contact for understandability; may require assistive technology | See Section 10 Statistical Considerations                     |
| Dyspnea                                                                                                                                                                         |                                                               |
| Grade 1 Shortness of breath with moderate exertion                                                                                                                                     | None                                                          |
| Grade 2 Shortness of breath with minimal exertion; limiting instrumental ADL                                                                                                           | None                                                          |
| Grade 3 Shortness of breath at rest; limiting self care ADL                                                                                                                            | See Section 10 Statistical Considerations                     |
| Grade 4 Life-threatening consequences; urgent intervention indicated                                                                                                                   | Termination of trial with reporting of dose limiting toxicity |
| Grade 5 Death                                                                                                                                                                          | Termination of trial with reporting of dose limiting toxicity |
| Stridor                                                                                                                                                                         |                                                               |
| Grade 3 Respiratory distress limiting self care ADL; medical intervention indicated                                                                                                    | See Section 10 Statistical Considerations                     |
| Grade 4 Life-threatening airway compromise; urgent intervention indicated (e.g., tracheotomy or intubation)                                                                            | Termination of trial with reporting of dose limiting toxicity |
| Grade 5 Death                                                                                                                                                                          | Termination of trial with reporting of dose limiting toxicity |
| Cough                                                                                                                                                                           |                                                               |
| Grade 1 Mild symptoms; nonprescription intervention indicated                                                                                                                          | None                                                          |
| Grade 2 Moderate symptoms, medical intervention indicated; limiting instrumental ADL                                                                                                   | None                                                          |
| Grade 3 Severe symptoms; limiting self care ADL                                                                                                                                        | See Section 10 Statistical Considerations                     |
| Myelitis                                                                                                                                                                        |                                                               |
| Grade 1 Asymptomatic; mild signs (e.g., Babinski's reflex or Lhermitte's sign)                                                                                                         | None                                                          |
| Grade 2 Moderate weakness or sensory loss; limiting instrumental ADL                                                                                                                   | None                                                          |
| Grade 3 Severe weakness or sensory loss; limiting self care ADL                                                                                                                        | See Section 10 Statistical Considerations                     |
| Grade 4 Life-threatening consequences; urgent intervention indicated                                                                                                                   | Termination of trial with reporting of dose limiting toxicity |
| Grade 5 Death                                                                                                                                                                          | Termination of trial with reporting of dose limiting toxicity |
| Skin and Subcutaneous Disorders                                                                                                                                                 |                                                               |
| Grade 1 Asymptomatic or mild symptoms; clinical or diagnostic observations only; intervention not indicated                                                                            | None                                                          |
| Grade 2 Moderate; minimal, local or noninvasive intervention indicated; limiting age-appropriate instrumental ADL                                                                      | None                                                          |
| Grade 3 Severe or medically significant but not                                                                                                                                        | See Section 10 Statistical Considerations                     |

|                                                                                                                                        |                                                               |
|----------------------------------------------------------------------------------------------------------------------------------------|---------------------------------------------------------------|
| immediately life-threatening; hospitalization or prolongation of existing hospitalization indicated; disabling; limiting self care ADL |                                                               |
| Grade 4 Life-threatening consequences; urgent intervention indicated                                                                   | Termination of trial with reporting of dose limiting toxicity |
| Grade 5 Death                                                                                                                          | Termination of trial with reporting of dose limiting toxicity |
| Injury to Carotid Artery                                                                                                        |                                                               |
| Grade 3 Severe symptoms; limiting self care ADL (e.g., transient cerebral ischemia); repair or revision indicated                      | See Section 10 Statistical Considerations                     |
| Grade 4 Life-threatening consequences; urgent intervention indicated                                                                   | Termination of trial with reporting of dose limiting toxicity |
| Grade 5 Death                                                                                                                          | Termination of trial with reporting of dose limiting toxicity |
| Hypothyroidism                                                                                                                  |                                                               |
| Grade 1 Asymptomatic; clinical or diagnostic observations only; intervention not indicated                                             | None                                                          |
| Grade 2 Symptomatic; thyroid replacement indicated; limiting instrumental ADL                                                          | None                                                          |
| Grade 3 Severe symptoms; limiting self care ADL; hospitalization indicated                                                             | See Section 10 Statistical Considerations                     |
| Grade 4 Life-threatening consequences; urgent intervention indicated;                                                                  | Termination of trial with reporting of dose limiting toxicity |
| Grade 5 Death                                                                                                                          | Termination of trial with reporting of dose limiting toxicity |
| Hypoparathyroidism                                                                                                              |                                                               |
| Grade 1 Asymptomatic; clinical or diagnostic observations only; intervention not indicated                                             | None                                                          |
| Grade 2 Moderate symptoms; medical intervention indicated                                                                              | None                                                          |
| Grade 3 Severe symptoms; medical intervention or hospitalization indicated                                                             | See Section 10 Statistical Considerations                     |
| Grade 4 Life-threatening consequences; urgent intervention indicated                                                                   | Termination of trial with reporting of dose limiting toxicity |
| Grade 5 Death                                                                                                                          | Termination of trial with reporting of dose limiting toxicity |

Dose limiting toxicities (DLT) will be defined as occurring whenever any one of the following are manifested as occurring whenever any one of the following are manifested: laryngeal edema (grade 4 or 5), dyspnea (grade 4 or 5), stridor (grade 4 or 5) probably or definitely related to the protocol.

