**Phase I**

Patients in each dose cohort will all be treated as a single group for fraction reduction. The starting dose will be 3.33 Gy per fraction for 15 fractions (total dose = 50 Gy). Subsequent cohorts of patients will receive a biologically equivalent dose delivered in 5 fewer fractions per step. If significant toxicity is encountered at the starting dose, an increase in fraction step will occur (step -1) to 3.28 Gy per fraction for 16 fractions (total dose 55 Gy).

| Step No. | Fractions | Dose per fraction (Gy) | Total Dose (Gy) | No. Patients |
|-----------------|------------------|-------------------------------|------------------------|---------------------|
| -1              | 16               | 3.28                          | 52.5                   | 3                   |
| 0 (starting)    | 15               | 3.33                          | 50.0                   | 3-15                |
| 1               | 10               | 4.50                          | 45.0                   | 7-15                |
| 2               | 5                | 8.50                          | 42.5                   | 7-15                |

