Stereotactic body radiation therapy (SBRT) is a new therapeutic paradigm for treating localized tumors outside of the central nervous system and involves delivering very high doses of focused radiation using unique beam arrangements and special immobilization equipment. As already demonstrated in lung and liver cancers, these treatments offer hope for improved local control of cancers that may translate into gains in survival especially for smaller early stage lesions. SBRT employs daily treatment doses dramatically higher than typical for conventionally fractionated radiation therapy (CFRT). In turn, it is incorrect to assume that SBRT radiobiology is similar to historical CFRT. Indeed, a unique biology of radiation response for very large dose per fraction treatments is being appreciated both in terms of tumor control as well as normal tissue consequences translating into unique clinical outcomes. For example, local control with CFRT in early stage lung cancer is consistently reported below 50% while several series using SBRT show local control around 90%.

SBRT has been defined by the American College of Radiology (ACR) and American Society of Therapeutic Radiology and Oncology (ASTRO) to involve the use of very large dose per fraction. Indeed, dose per fraction of 6 Gy minimum would obviously make SBRT very different from even the more abbreviated hypofractionation schemes described above. Typically, only 1-5 fractions are used for SBRT depending on the tolerance of adjacent or intervening normal tissues. Linear structures (like the spinal cord) and tubular structures (like the bowels) are commonly called “serially functioning tissues” akin to series electrical circuits because their function is disrupted if there is a defect anywhere along their pathways. It has been shown that serial functioning tissues are less tolerant to SBRT than so-called “parallel functioning tissues” like the peripheral lung and liver. In response, typically more fractions are employed (e.g., five fractions rather than one) when serially functioning tissue cannot be avoided.

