### 1.3 Current Protocol

There are multiple therapeutic options for early-stage glottic larynx cancer with similarly high local control and overall survival rates as mentioned above. However, surgical approaches are invasive and may have worse voice outcomes, while conventional radiation therapy is inconvenient and treats large volumes of uninvolved normal tissue. Using CyberKnife-based SBRT, this protocol will spare adjacent uninvolved normal tissue for the purpose of decreasing the number of fractions required for curative treatment.

As surgical ablation and resection have excellent local control and cure rates for early stage glottis larynx cancer, the “radiosurgery” volumes will emulate volumes of tissue

typically removed or ablated during surgery. Thus, the radiation volume will approximate CO2 laser excision for carcinoma *in situ* and cT1 lesions which typically includes 2 mm of adjacent vocal cord, and the radiation volume for T2 lesions will emulate volumes of tissue typically removed during voice preserving hemilaryngectomy.

Through hypofractionated SBRT with geometric avoidance of uninvolved normal tissue, we aim to increase convenience, decrease toxicity, and improve local control compared to other methods of radiation treatment. As SBRT is a local treatment, eligible patients will be limited to early-stage laryngeal cancer defined as AJCC Tis, T1, and T2 lesions that have less than a 5% risk of nodal or distant metastases at diagnosis.

The feasibility of reducing fractions in early-stage laryngeal cancer has not previously been prospectively studied, and we will therefore conduct a careful phase I bio-equivalent dose fraction reduction study. Patients enrolled at each dose level will undergo routine evaluations to identify potential toxicities as well functional voice analyses. Adequate waiting periods will be used to ensure that fraction reduction does not proceed prior to observing toxicity. The purpose of the study will be either to determine the maximal fraction reduction possible until a dose is reached where a dose-limiting toxicity occurs. The initial dose and fractionation will be 50 Gy in 15 fractions with the goal to reduce number of fractions to a dose of 42.5 Gy in 5 fractions. The rationale for using 5 fractions is that it is tolerated in centrally located lung tumors at a dose of 50 Gy in 5 fractions, and thus, is likely to be tolerated in large caliber airways.

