#### cT2 lesions

The gross tumor volume (GTV) and internal target volume (ITV) will be contoured based upon 4-D respiratory gated CT-scan. The clinical target volume (CTV) will include the ITV plus a 2 mm geometric expansion that may be modified at the discretion of the treating physician, entire ipsilateral vocal cord, and ipsilateral paraglottic space. For lesions coming within 2 mm of or involving the ipsilateral arytenoid, the arytenoid will be included in the CTV. For lesions located within 2 mm of the anterior commissure or involving the anterior commissure, the CTV will include the anterior commissure as well as 2 mm of the adjacent contralateral vocal cord. The PTV will be the CTV plus a 3 mm uniform expansion in all directions.

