#### 4.5 Dose Constraints

| OAR           | Volume | Dose          |
|----------------------|---------------|----------------------|
| Thyroid              | Mean          | <10% prescribed dose |
| Right carotid artery | Maximum point | <10% prescribed dose |
| Left carotid artery  | Maximum point | <10% prescribed dose |
| Spinal cord          | Maximum point | <5% prescribed dose  |
| Skin                 | Maximum point | <10% prescribed dose |

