## 9.0 QUALITY OF LIFE AND COST-EFFECTIVENESS

### 9.1 Health-Related Quality of Life (HRQOL) Analysis

The study design is to prospectively analyze the HRQOL among patients with early stage glottis cancer who are treated on this protocol. While hypofractionation is hypothesized to yield greater tumor cell kill, it may also increase the normal tissue toxicity, in which case there may be a decrease in HR-QOL. The primary normal tissue toxicities in patients receiving radiation

depends on the location of the treatment. Prior studies have demonstrated that the most sensitive and clinically meaningful method for accurately capturing the normal tissue toxicities is via patients reported outcomes (PROs), such as HRQOL.

In this non-randomized trial, we plan to assess the HR-QoL forms at specific time points to minimize patient burden: baseline (pretreatment), at the end of radiation, and at subsequent follow ups (See Appendix).

In addition, the EQ-5D will be used as well. EQ-5D is a standardized instrument for use as a measure of health outcome. Applicable to a wide range of health conditions and treatments, it provides a simple descriptive profile and a single index value for health status. The US version of the EQ-5D will be used, to enable mapping of general HR-QoL scores from EQ-5D scores into health state utility scores (ranging from 0 to 1) for the US population. These utility scores are needed for cost-utility analysis (estimates of costs per “quality adjusted” life-year gained).

HRQoL of patients with early stage glottis cancer is fortunately well documented but there exist wide variability in the forms used to assess HR-QoL and the majority of HR-QoL being reported for traditional fractionated radiotherapy, surgery, or laser techniques.

In a study from the Czech Republic evaluating the health-related quality of life of patients treated with either radiotherapy or endoscopic trans oral into laryngeal surgery, the authors concluded that was no difference between patients treated with the cordectomy and radiotherapy. They assessed health related quality of life using the EORTC-QLQ C30 and H&N 35 forms.

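### 42.5 Gy in 5 fractions is called bio-equivalent with no tissue, model or alpha/beta named; the label is unsupported for in-field late-reacting laryngeal tissue and model-dependent for tumour

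*Protocol*

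**What the plan says.** The equivalence wording appears in three places:

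- Schema, Phase I: "Subsequent cohorts of patients will receive a biologically equivalent dose delivered in 5 fewer fractions per step".
- Section 1.3: "we will therefore conduct a careful phase I bio-equivalent dose fraction reduction study".
- Section 4.1, which names the level 2 dose: "there will be an additional reduction to 5 fractions to a bio-equivalent dose of 42.5 Gy".

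The schedules, from the dose table in section 4.1, are 50 Gy in 15 (level 0), 45 Gy in 10 (level 1) and 42.5 Gy in 5 (level 2), given 5, 3 and 2 times a week. None of the three places states a BED, a formula, an alpha/beta or the tissue meant.

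Other text bears on the point. Section 1.3 supports five fractions by analogy with the airway: "it is tolerated in centrally located lung tumors at a dose of 50 Gy in 5 fractions". Section 1.2 warns that "it is incorrect to assume that SBRT radiobiology is similar to historical CFRT". Section 9.1 says of hypofractionation that "it may also increase the normal tissue toxicity". For cT2 lesions, section 4.3 puts the "entire ipsilateral vocal cord, and ipsilateral paraglottic space" inside the clinical target volume. Section 4.5 holds each carotid artery and the skin to a maximum point dose of "<10% prescribed dose", and the spinal cord to half that share.

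**The concern.** From level 1 to level 2 the dose per fraction nearly doubles, from 4.5 to 8.5 Gy, while the total falls by only 2.5 Gy. Under the usual fractionation models that does not hold biological effect constant in tissue sensitive to fraction size. The label therefore asserts a property that the schedule may lack in the tissue at full dose.

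Two things are at stake. First, section 10.1 frames the endpoint as the smallest tolerated number of fractions. If level 2 fails, an equivalence label invites the conclusion that five fractions are too few, when the schedule may also carry a higher biological dose. Second, the excess matters most for late effects. Late toxicity (from about 18 months) is only a secondary objective, while each step is gated on 90 days. A reader told that the dose is equivalent has less reason to look for a late difference.

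**Working it through.** **Inputs from the protocol (section 4.1 table).** Total dose D and fractions n: level -1 52.5/16, level 0 50/15, level 1 45/10, level 2 42.5/5. For level -1 both dose tables give 52.5 Gy, which agrees with 16 × 3.28; the Schema's running text prints 55 Gy, which is not used here.

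**Assumptions (not in the protocol).** Alpha/beta 3 Gy for late-reacting tissue and 10 Gy for tumour, with 2 and 15 as wider limits; the LQ-L transition dose dT; no repopulation term. Nominal durations are 15/5 = 3, 10/3 = 3.3 and 5/2 = 2.5 weeks.

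The protocol gives no BED, so there is no stated figure to reproduce first.

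**1. LQ.** With d = D/n, BED = D(1 + d/(α/β)) = D + (D²/n)/(α/β). D²/n is 166.67, 202.5 and 361.25 for levels 0, 1 and 2.

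| α/β | Level 0 | Level 1 | Level 2 | 1 vs 0 | 2 vs 0 |
|---|---|---|---|---|---|
| 2 | 133.3 | 146.25 | 223.1 | +9.7% | +67% |
| 3 | 105.6 | 112.5 | 162.9 | +6.6% | +54% |
| 10 | 66.7 | 65.25 | 78.6 | -2.1% | +18% |
| 15 | 61.1 | 58.5 | 66.6 | -4.3% | +9% |

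Example at 3: level 0 is 50 + 166.67/3 = 105.6; level 2 is 42.5 + 361.25/3 = 162.9; the ratio is 1.54.

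**2. Which alpha/beta would make the levels equal under LQ?**

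- Levels 0 and 1: (202.5 - 166.67)/(50 - 45) = 7.2 Gy.
- Levels 0 and 2: (361.25 - 166.67)/(50 - 42.5) = 25.9 Gy.
- Levels 1 and 2: (361.25 - 202.5)/(45 - 42.5) = 63.5 Gy.

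No single value makes all three equal.

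**3. LQ-L with tangent slope.** For d > dT, BED = n[dT(1 + dT/(α/β)) + (1 + 2dT/(α/β))(d - dT)].

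| dT (Gy) | α/β 3: level 0, level 2 | Difference | α/β 10: level 0, level 2 | Difference |
|---|---|---|---|---|
| 3 | 105.0, 112.5 | +7% | 66.5, 63.5 | -5% |
| 4 | 105.6, 129.2 | +22% | 66.7, 68.5 | +3% |
| 5 | 105.6, 142.5 | +35% | 66.7, 72.5 | +9% |
| 7 | 105.6, 159.2 | +51% | 66.7, 77.5 | +16% |

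Example at dT 4 and α/β 3: 5[4(1 + 4/3) + (1 + 8/3)(4.5)] = 5(9.33 + 16.5) = 129.2.

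**4. A shallower high-dose slope.** At dT 4 and α/β 3 the tangent slope is 1 + 8/3 = 3.67. With slope 2.5, level 2 is 5(9.33 + 2.5 × 4.5) = 102.9, or -2.5%. With slope 2 it is 5(9.33 + 9) = 91.7, or -13%. So a free slope can remove the late-tissue excess or reverse it.

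**5. Organs held to the section 4.5 caps (LQ).** At a share f of prescription, BED = fD(1 + fd/(α/β)).

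- Carotid and skin, f = 0.10: level 0 vs level 2 is 5.56 vs 5.45 Gy (-2%) at α/β 3, and 5.83 vs 6.06 (+4%) at 2.
- Spinal cord, f = 0.05: 2.64 vs 2.43 (-8%) at 3, and 2.71 vs 2.58 (-5%) at 2.

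The excess therefore concerns tissue at or near prescription dose, not these organs.

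**The case against.** The strongest reply is that nothing has been miscalculated. The protocol prints no BED, and every parameter above is the reviewer's. That stands: the fault is an unqualified label, not a wrong sum.

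The label can also be defended for tumour effect. Sections 1.3 and 1.4 speak of curative treatment and of maintaining local control. At α/β 10 and dT 4 Gy, level 1 is 10[4(1.4) + 1.8(0.5)] = 65.0 (-2.5%) and level 2 is 68.5 (+3%), so all three levels lie within about 3%. That also stands, and it is why tumour equivalence is called model-dependent rather than wrong. But the protocol does not limit the label to tumour. The caution in section 1.2 supplies no other model that would support it.

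The protocol does not run level 2 as equal in toxicity. Its table is headed as a dose escalation and prints 8.5 Gy per fraction. Dexamethasone is added at levels 1 and 2, the weekly rate slows, the minimum cohort rises from 3 to 7, and section 9.1 concedes possible added toxicity. Section 10.1 names the schedule itself. Section 1.3 leans on 50 Gy in 5 in the central lung, which at α/β 3 under LQ is 50(1 + 10/3) = 216.7 Gy, above level 2's 162.9. These facts soften the harm, and the rationale for five fractions does not need the word. None of them corrects it.

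Three stronger inferences are tempting and unsupported:

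- A reader might take 22% to 54% as bounds for late tissue, or 3% to 18% for tumour. The lower ends hold only for a tangent slope with transition at 4 Gy or more. At 3 Gy they fall to +7% and -5%.
- A reader might expect a matching rise in dose-limiting events within 90 days. Those are mostly early reactions, which an alpha/beta of 3 does not describe.
- A reader might conclude that level 2 is unsafe. BED is not a toxicity rate, and no such conclusion follows.

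**Conclusion.** The point holds in limited form. As written, the equivalence label for 42.5 Gy in 5 fractions is unsupported for late-reacting laryngeal tissue inside the target. Level 2 exceeds level 0 by 54% under LQ and by 7% to 51% under tangent-slope LQ-L with dT 3 to 7 Gy, at assumed α/β 3. For tumour at assumed α/β 10 the difference runs from -5% to +18% across the same models, so equivalence is arguable but needs its model stated. The label fits level 1 (within about 10% under LQ for α/β 2 to 15).

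All of this rests on assumed parameters and omits repopulation, and a shallower high-dose slope would remove the late-tissue excess. Severity is minor: the consequence is for interpreting late toxicity and for attributing a level 2 result to fraction number, not for the doses or the step rules.

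**What to change.** 1. In the Schema, section 1.3 and section 4.1, drop *bio-equivalent* for level 2. Alternatively, limit it to tumour effect and print the model and alpha/beta used.
2. Add two BED columns to the section 4.1 dose table, marked as LQ with assumed α/β 10 and 3: level -1 69.7/109.9, level 0 66.7/105.6, level 1 65.25/112.5, level 2 78.6/162.9 Gy. Add a note that LQ may overstate the effect at 8.5 Gy per fraction.
3. In section 10.1, state that level 2 results, tolerated or not, are reported for the schedule of 42.5 Gy in 5 fractions and not as the effect of fraction number at equal biological dose.

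The cost is wording in four sections and two table columns. There are no extra patients or visits, and no change to doses or stopping rules. The downside is a less favourable presentation of level 2 to the monitoring committee and ethics board.
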